### Study withdrawal

Given that the primary and secondary outcomes require the presence of a catheter, follow up for these outcomes can only occur if the patient is alive, accessible for monitoring, and has a catheter in-situ. Therefore patients will be censored and withdrawn from follow-up at the following points in time: removal of the catheter (including accidental removals and exchange over a guidewire); a non-mechanical indication (such as catheter-related infection, transfer to peritoneal dialysis, kidney transplantation, maturation of permanent access, or withdrawal from therapy); transfer of patient to another city which is not a satellite unit of the original study centre; and death.

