### Primary outcome

The primary outcome is catheter malfunction, defined by one of the following events occurring after attempts to re-establish patency have been undertaken as per a pre-defined protocol (including flushing the catheter with a 10 cc syringe, repositioning the patient and reversal of lines):

• Peak blood flow ≤ 200 ml/min for 30 minutes during an ongoing dialysis treatment (with maximum arterial and venous pressure limits of -250 mmHg and +250 mmHg respectively)

• Mean blood flow ≤ 250 ml/min during two consecutive dialysis sessions, calculated as the blood processed in millilitres divided by the time on dialysis in minutes (with maximum arterial and venous pressure limits of -250 mmHg and +250 mmHg respectively)

• Inability to initiate dialysis with no blood flow

According to the K/DOQI guidelines an extracorporeal blood flow of ≥ 300 ml/min is required to provide adequate dialysis [7]. A peak blood flow of ≤ 200 ml/min for 30 minutes, or a mean blood flow of ≤ 250 ml/min during two consecutive dialysis sessions, were chosen to define catheter malfunction as this blood flow will not permit achievement of adequate dialysis. The blood flow must be maintained with a maximum venous pressure of +250 mmHg and arterial pressure of -250 mmHg, to ensure higher blood flows are not achieved at the expense of excessive pressures. A blood flow which cannot be maintained with venous and arterial pressures of 250 mmHg should be investigated for catheter malfunction.

Reversal of catheter lines may be required to initiate or maintain dialysis during some sessions, however reversal of lines over several sessions may lead to increased re-circulation of blood and inadequate dialysis. The need for ongoing reversal of catheter lines to maintain dialysis would therefore suggest potential malfunction. A protocol regarding catheter line reversal will be implemented to ensure that ongoing line reversal is not undertaken, specifically:

• Catheter lines may be reversed in an attempt to re-establish patency and initiate/maintain dialysis

• Catheter lines may be reversed for **no more than three consecutive** dialysis sessions

• After three consecutive dialysis sessions with reversed lines **the next two consecutive** sessions must be run with lines in the straight position. Primary outcomes will then be assessed

• Primary outcome criteria is the same during the period of line reversal

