### Sample size considerations

Sample size calculations are based on dropout rates and time to needing rt-PA for catheter malfunction as observed at the University Health Network in Toronto, Canada ([name] personal communication), as well as reported by Little et al [13]. The following parameters were used for the sample size calculations: annual dropout rate of 75%; one year event rate in the heparin arm of 95% and 98%; effect sizes of 30%, 33.3%, 35% and 40%; power of 0.80; and an α-level of 0.05. Calculations were done using simulations with 500 samples per condition, and assuming the dropout rate was independent of the primary outcome. Simulations including virgin versus non-virgin catheter status had no appreciable impact on sample size estimates. Table 5 presents the number of patients required per arm to detect specified risk reductions, at failure rates of 95% and 98% respectively. Given these estimates a study size of 170 patients per arm was chosen.

**Table 5 T5:** Number of patients per arm, based on effect size and failure rate

**Effect Size**	**Failure Rate 95%**	**Failure Rate 98%**
**30%**	235	195
**33.3%**	185	160
**35%**	160	140
**40%**	120	95

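### As printed, a catheter removed or exchanged for poor function before it meets a flow criterion is censored, not counted as malfunction, and no rule provides otherwise

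*Protocol article*

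**What the plan says.** The Study withdrawal section lists the points at which patients are censored and leave follow-up. The first is "removal of the catheter (including accidental removals and exchange over a guidewire"), with no reason attached. After a semicolon comes an item on non-mechanical indications, with infection, transplantation and a matured permanent access among its examples. Transfer to another city and death complete the list.

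The Primary outcome section defines catheter malfunction by three flow criteria, each applied after set attempts to restore patency:
- peak flow of 200 ml/min or less for 30 minutes;
- mean flow of 250 ml/min or less in two consecutive sessions;
- no flow, so that dialysis cannot start.

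Removal or exchange for malfunction is not among them. The same section cites guidance that "an extracorporeal blood flow of ≥ 300 ml/min is required to provide adequate dialysis".

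The Sample size considerations section bases its simulations on "one year event rate in the heparin arm of 95% and 98" per cent, an "annual dropout rate of 75" per cent, "effect sizes of 30%, 33.3%, 35% and 40" per cent, and "power of 0.80; and an α-level of 0.05", "assuming the dropout rate was independent of the primary outcome". From these, "a study size of 170 patients per arm was chosen".

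**The concern.** There is a gap between a catheter working poorly and a catheter meeting a criterion. The mean-flow criterion needs two consecutive sessions, so removal after one poor session falls before the event. A catheter with mean flow between 250 and 300 ml/min is below the cited adequacy level but meets no mean-flow criterion, and it too may be replaced. The protocol expects such replacements in general: the baseline data in Table 3 include past catheter replacement for malfunction, and the main objective of the cost-effectiveness analysis is the cost of avoiding a new catheter.

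If such a removal is censored, the patient leaves the risk set because the catheter is failing. The Kaplan-Meier and Cox analyses in the Statistical analysis section then treat that patient as having the same future risk as those who remain, which is unlikely. At stake are the number of events, the absolute malfunction rates and, if removals of this kind take a different share of malfunctions in each arm, the hazard ratio itself.

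**Working it through.** **1. The rules side by side.**

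| Course of the catheter | Counted as |
|---|---|
| Meets a flow criterion, later removed | Event (follow-up continues for a further month, or until recovery or removal) |
| No flow at start, or peak flow ≤ 200 ml/min for 30 minutes | Event; one session is enough |
| One session with mean flow ≤ 250 ml/min, then removed or exchanged for poor function | Censored as printed |
| Removed for a non-mechanical reason | Censored |

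Only the third row is at issue.

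**2. The plan's own sample size.** Inputs from Sample size considerations: one-year event rate 95% or 98%, dropout 75% a year, α 0.05, power 0.80. Follow-up is six months (Patient follow-up procedures). Three assumptions are mine: exponential times, a two-sided test, and effect size read as hazard reduction.

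- Event hazard: λ = −ln(1 − 0.95) = 2.996 per year. Dropout hazard: μ = −ln(1 − 0.75) = 1.386 per year.
- P(event) = λ/(λ+μ) × [1 − exp(−0.5(λ+μ))].
- Heparin: 2.996/4.382 × (1 − 0.112) = 0.607. rt-PA at HR 0.65 (λ = 1.947): 1.947/3.334 × (1 − 0.189) = 0.474.
- Freedman's formula: events = (1.960 + 0.842)² × (1.65/0.35)² ≈ 174, so n per arm ≈ 174/(0.607 + 0.474) ≈ 162, against 160 in Table 5.

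| Effect | 95%: stated / Freedman | 98%: stated / Freedman |
|---|---|---|
| 30% | 235 / 230 | 195 / 200 |
| 33.3% | 185 / 181 | 160 / 158 |
| 35% | 160 / 162 | 140 / 141 |
| 40% | 120 / 120 | 95 / 104 |

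The last cell has simulated power 0.782, within the error of 500 simulations (standard error √(0.8 × 0.2/500) ≈ 0.018). The table reproduces, so the model is a fair base.

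**3. Effect of the censoring rule.** Let q be the share of malfunctions removed or exchanged before a criterion is met. The protocol gives no value; the range of 0 to 30% is assumed. Moving that share of the event hazard to censoring gives:

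- events = 170 × [0.607(1 − q_hep) + 0.474(1 − q_rtPA)];
- observed HR = 0.65 × (1 − q_rtPA)/(1 − q_hep);
- power = Φ(√(events/4) × |ln HR| − 1.96) (Schoenfeld).

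| q heparin / rt-PA | Events | Observed HR | Power |
|---|---|---|---|
| 0 / 0 | 184 | 0.65 | 83% |
| 10% / 10% | 165 | 0.65 | 79% |
| 20% / 20% | 147 | 0.65 | 74% |
| 30% / 30% | 129 | 0.65 | 69% |
| 10% / 5% | 169 | 0.69 | 69% |
| 5% / 10% | 171 | 0.62 | 89% |

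For 10% / 5%: HR = 0.65 × 0.95/0.90 = 0.686, and √(169.4/4) × 0.377 − 1.96 = 0.49, so power is 69%.

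With the 33.3% effect, power starts at 79% and falls to 74%, 69% and 64% at equal loss of 10%, 20% and 30%. With the 98% event rate and HR 0.65, it starts at 88% and falls to 84%, 80% and 75%.

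**4. Absolute rates.** The six-month Kaplan-Meier malfunction estimate in the heparin arm is 1 − exp(−0.5 × 2.996 × (1 − q)): 77.6% at q = 0, and 74.0%, 69.8% and 65.0% at 10%, 20% and 30%.

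**5. Type I error.** Under no true effect (log-rank simulation, 4,000 runs per case), equal loss of 10% or 20% gives 0.048 or 0.045. Unequal loss of 10% against 5% gives 0.069, with mean HR 1.05 when the larger loss is in the heparin arm and 0.95 when it is in the rt-PA arm.

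**The case against.** **The non-mechanical item may be a displaced qualifier.** It is not itself a point in time, and it may have been meant to limit the removals that are censored. This is plausible, and the text does not settle it. It does not close the gap: under that reading a mechanical removal before a criterion is met is neither a listed event nor a listed censoring point.

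**Most failing catheters are counted.** This stands. Two criteria can be met in one session, so the most severe failures are largely captured. Not counting flows between 250 and 300 ml/min in a catheter that stays in place follows from the chosen threshold, not from the censoring rule.

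**Bias is not shown.** This also stands. A reader might infer that heparin, with more malfunctions, must lose more events and that the hazard ratio therefore moves toward 1. A larger number of malfunctions is simply the treatment effect; the ratio shifts only if the share lost differs. Blinding of patients, providers and assessors, together with a common patency protocol, makes a large difference less likely, though it does not exclude one.

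**Independent dropout is only a simulation assumption.** True, but the planned survival analyses need the same condition.

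**Conclusion.** The point holds in a limited form. As printed, removal or exchange for poor function before a flow criterion is met is censored, and this is plausibly informative. On the alternative reading of the list, no rule covers such a removal.

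The size depends on a share that the protocol does not give. On the exponential model, with the 95% event rate and HR 0.65, equal loss of 10% to 30% costs about 4 to 15 points of power and lowers the estimated six-month heparin malfunction rate by about 4 to 13 points. It leaves the hazard ratio and the type I error essentially intact.

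Two stronger readings are not supported. One is that any failing catheter that is pulled becomes a non-event: those that meet a criterion first are events. The other is that the primary comparison is necessarily biased: that requires a difference between arms, which the document neither shows nor rules out and which could favour either arm.

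**What to change.** Before unblinding, reconcile the Primary outcome and Study withdrawal sections:

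- Limit censoring at removal to accidental removal and to removal or exchange for a non-mechanical reason.
- Record the reason for every removal or exchange, classified blind to allocation.
- Count removal or exchange for documented catheter malfunction as an event on the date of removal, and report the flow-criteria-only definition alongside. The reverse is also acceptable: keep the flow criteria as primary and pre-specify the removal-inclusive definition as a sensitivity analysis.

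The cost is a sentence or two in the outcome and withdrawal rules, one field on the electronic case report form, and one further analysis. The downside is small: the reason for removal needs blinded classification and brings some judgement into an endpoint otherwise based on measured flow. The choice has to be made before unblinding, because deciding afterwards which removals are events would be post hoc.

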### Statistical analysis

Analysis of the primary and secondary outcomes will be based on the intention-to-treat principle. Individual primary outcomes, in addition to the composite outcomes, will be examined. The time from randomization until catheter malfunction will be analyzed and Kaplan-Meier estimates of the probability of event-free survival will be calculated for the control and treatment arms. Cox proportional hazards analysis will also be used to compare event-free survival in the rt-PA and heparin groups, controlling for clinical risk factors and including stratification variables. A secondary on-treatment analysis will also be undertaken. A planned subgroup analysis will be undertaken stratified by catheter luminal volume. This analysis will take into account the actual concentration of rt-PA the patient received as the luminal volume, and thus rt-PA concentration, may vary between patients.

The proportion of patients in each treatment arm achieving the secondary outcome, catheter-related bacteremia, will be determined, as will the number of infections per 1000 catheter-days. Differences in proportions will be assessed using the Fisher's exact test and the number of infections per 1000 catheter days using the exact binomial test. A secondary analysis to identify predictors of catheter malfunction, including variables such as intra-dialysis weight loss and catheter flow parameters, will also be conducted.

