More recently tissue plasminogen activator (rt-PA) has been used in the treatment of catheter-related thrombosis [13-16], and has also been considered as a possible locking solution for the primary prevention of catheter malfunction. Rt-PA preferentially binds to fibrin and thus activates plasminogen in close proximity to the clot, which confines fibrinolysis to the formed thrombus and, in theory, avoids systemic activation. Using a randomized crossover design with 12 patients, Schenk and colleagues [17] demonstrated that use of 2 mg of rt-PA per catheter lumen at the end of each hemodialysis session was superior to the conventional practice of locking each lumen with 2000 units of heparin. After four months, 20% of the heparin locked catheters had a thrombotic event versus 0% in the rt-PA group. While the results of this study are encouraging with respect to rt-PA as a catheter locking solution, the small sample size and single centre enrolment limit the study generalizability and the ability to change clinical practice based on these results. In addition, the cost of using rt-PA after each dialysis session may out-weigh the potential benefit.

The optimal frequency of instillation and dose of rt-PA in the primary prevention of catheter malfunction is unknown. In the study by Schenk et al [17] the dose of rt-PA was 2 mg per lumen (information regarding luminal volume was not provided), instilled after each dialysis session. It may be possible that a smaller dose, such as 1 mg per lumen, or less frequent administration, such as once every week, may result in a decreased incidence of catheter malfunction when compared to the standard instillation of heparin, at a more reasonable cost.

In addition to thrombosis, catheter-related bacteremia is a serious complication of catheter use, with a reported incidence of 2.5 to 6.5 episodes per 1000 catheter-days [18-21]. Several mechanisms are believed to contribute to catheter-related bacteremia, including the formation of an intraluminal thrombosis which may act as a nidus for bacterial biofilm development on the catheter [22,23]. While antibiotic locking solutions have been proposed as a method to treat (.([24], as well as prevent [25], catheter-related bacteremia, their side effects limit their wide-spread use [26]. It is plausible that use of a locking solution which decreases the rate of thrombus formation consequently may also decrease the rate of catheter-related bacteremia [26].

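### Kaplan-Meier "event-free survival" censors exits that preclude malfunction, so it does not give the share of randomised patients whose catheter malfunctions; cumulative incidence should be added.

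*Protocol article*

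**What the plan says.** The Statistical analysis section takes time from randomization to catheter malfunction as the primary analysis variable. It states that "Kaplan-Meier estimates of the probability of event-free survival will be calculated for the control and treatment arms", with Cox regression for the comparison. It names no other absolute-risk estimate for the primary outcome.

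The Study withdrawal section reasons that both outcomes can be observed only while a catheter is in place. It continues: "Therefore patients will be censored and withdrawn from follow-up at the following points in time". The list that follows covers catheter removal, non-mechanical reasons (infection, peritoneal dialysis, transplantation, maturation of permanent access, withdrawal from therapy), transfer to another city, and death.

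The Sample size considerations section plans for an "annual dropout rate of 75" per cent, without a breakdown by reason. Its simulations were run "assuming the dropout rate was independent of the primary outcome".

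**The concern.** Most of the listed exits do more than end observation. A patient who dies, is transplanted or moves to a working fistula can no longer have a malfunction of that catheter. Kaplan-Meier treats such a patient as someone who would have gone on to malfunction at the same rate as those still at risk.

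Two consequences follow.

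- The label is wrong. A curve that censors deaths is not event-free survival.
- One minus the curve is larger than the proportion of randomised patients who malfunction.

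Heavy dropout makes the second point matter. A 75% annual rate means that about half of patients would leave within six months in the absence of malfunction. A reader who takes six-month risks from the curve would take risks that are too high in both arms.

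**Working it through.** **Inputs, all from Sample size considerations unless noted**

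- Heparin arm: "one year event rate in the heparin arm of 95% and 98" per cent. As a constant yearly hazard, λ = −ln(1 − p): −ln(0.05) = 2.996 and −ln(0.02) = 3.912.
- Dropout 75% per year: δ = −ln(0.25) = 1.386. Over six months, 1 − exp(−0.5 × 1.386) = 50%.
- Effect: "effect sizes of 30%, 33.3%, 35% and 40" per cent, read as hazard ratio = 1 − effect. I use 0.65 for illustration.
- Horizon: t = 0.5 year (Patient follow-up procedures).
- "power of 0.80; and an α-level of 0.05", taken as two-sided.

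**Step 1. Does this model match the protocol's planning?** I used Freedman events, ((1+HR)/(1−HR))² × (1.960+0.842)², rounded up and divided by the sum of the two arms' probabilities of an observed event by six months. For HR 0.65 at the 95% rate: 175 / (0.607 + 0.474) = 162 per arm, against 160 in Table 5.

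| Effect | 95%: Table 5 | 95%: recomputed | 98%: Table 5 | 98%: recomputed |
|---|---|---|---|---|
| 30% | 235 | 230 | 195 | 200 |
| 33.3% | 185 | 181 | 160 | 158 |
| 35% | 160 | 162 | 140 | 141 |
| 40% | 120 | 120 | 95 | 104 |

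Seven of eight cells agree within 3% or 2 patients. Simulated log-rank power at the stated sizes is 0.78 to 0.82 throughout, in line with the noise of 500 samples (standard error about 1.8 points). So 95% and 98% act as rates without dropout, and the 75% acts as separate independent censoring over six months.

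**Step 2. The two estimates at six months.** Let s be the share of the dropout hazard that is competing; the rest is ordinary censoring.

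- 1−KM = 1 − exp(−0.5λ)
- Cumulative incidence (CI) = λ/(λ + sδ) × [1 − exp(−0.5(λ + sδ))]

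Example, heparin at 95% with s = 1: 1 − exp(−1.498) = 77.6%, against 2.996/4.382 × [1 − exp(−2.191)] = 60.7%.

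For rt-PA, λ is multiplied by 0.65. Differences are taken before rounding.

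| Rate | s | Heparin 1−KM / CI (gap) | rt-PA 1−KM / CI (gap) | Risk difference, KM / CI |
|---|---|---|---|---|
| 95% | 1 | 77.6 / 60.7 (16.9) | 62.2 / 47.4 (14.8) | 15.4 / 13.3 |
| 95% | 0.5 | 77.6 / 68.4 (9.3) | 62.2 / 54.1 (8.2) | 15.4 / 14.3 |
| 95% | 0.25 | 77.6 / 72.8 (4.9) | 62.2 / 57.9 (4.3) | 15.4 / 14.8 |
| 98% | 1 | 85.9 / 68.6 (17.2) | 72.0 / 55.6 (16.3) | 13.9 / 13.0 |
| 98% | 0.5 | 85.9 / 76.5 (9.4) | 72.0 / 63.0 (9.0) | 13.9 / 13.5 |
| 98% | 0.25 | 85.9 / 80.9 (4.9) | 72.0 / 67.3 (4.7) | 13.9 / 13.7 |

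A simulation of 400,000 patients per setting gave crude six-month proportions of 60.7%, 47.4%, 68.7% and 55.7% for the four s = 1 entries, in agreement with the formula.

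**Step 3. What this does to the contrast.** If a number needed to treat were quoted, s = 1 would change it from 6.5 to 7.5 at the 95% rate (1/0.154 and 1/0.133) and from 7.2 to 7.7 at the 98% rate (1/0.139 and 1/0.130). At s = 0.5 the cumulative-incidence values are 7.0 and 7.4.

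**The case against.** The strongest reply is that the plan never promises what it is faulted for. The article does not say that one minus the curve will be read as the share of patients who malfunction, and it plans no number needed to treat. The Study withdrawal section explains why follow-up ends with the catheter. With independent censoring, malfunction-free function while a catheter remains in place is a coherent quantity. That stands, and it is why the Kaplan-Meier curve should be relabelled and kept. It does not rescue the present label, and it leaves the plan with no estimate of actual malfunction risk.

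A reader might also infer four stronger points that the documents do not support.

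- **That the overstatement is 15–17 points.** This is an upper bound. It needs every dropout to be competing, whereas transfer to another city is ordinary censoring and no split is given.
- **That the treatment comparison is invalid.** Cox regression with these exits censored compares cause-specific hazards, which is a legitimate comparison.
- **That the cost model would be biased.** The Cost-effectiveness analysis section does not say that Kaplan-Meier risks feed the model. A monthly Markov model with death as its own state needs transition probabilities conditional on a functioning catheter, which hazards with death censored supply.
- **That arm-specific censoring biases the result.** The Background says only that a lock which reduces thrombus "may also decrease the rate of catheter-related bacteremia". Infected patients stay in the study unless a new catheter is needed. Unequal censoring between arms does not by itself bias either method; dependence within an arm would, and that is not shown.

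**Conclusion.** The point holds as a matter of labelling and of absolute risk. The planned curve is not event-free survival, and its complement overstates the share of randomised patients who malfunction by six months. At a hazard ratio of 0.65 the overstatement per arm lies between about 4–5 points (a quarter of dropout competing) and 15–17 points (all of it). The between-arm difference shrinks by about 2 points at most.

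These sizes rest on constant hazards, on dropout independent of malfunction, on effect sizes read as hazard reductions, and on an assumed competing share that the article does not give. It is a worthwhile, inexpensive improvement to reporting and does not threaten the primary comparison.

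**What to change.** - Report six-month malfunction risk by arm as Aalen-Johansen cumulative incidence. Death, transplantation, change of modality, access maturation and non-mechanical catheter removal are the competing events; transfers to another city stay censored.
- Use these estimates for any absolute risk difference or number needed to treat that is stated.
- Rename the Kaplan-Meier curve malfunction-free catheter survival, and say that it assumes independent censoring.
- Tabulate exits by reason and arm, so that readers can see the competing share.
- Keep the Cox model as the treatment comparison.

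The cost is some wording, one figure and one table, from exit reasons that the withdrawal rules already require sites to identify. The quoted absolute benefit would be slightly smaller. Cumulative incidences also depend on local rates of transplantation, access maturation and other exits, so they carry over less directly to other settings.

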### Secondary outcome

Catheter-related bacteremia, the secondary outcome, will be defined according to the Canadian definitions for catheter-related infections [31], as outlined in Table 2. Both "definite" and "probable" infections will constitute a study outcome. These patients will remain in the study and their catheter-related infection will be treated by the attending staff nephrologist according to usual practice. If a new catheter is clinically indicated the patient will be censored at the time of catheter removal.

**Table 2 T2:** Definitions for catheter-related bacteremia

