### Patient follow-up procedures

Patients will be followed from trial entry until study completion (six month study period). The study coordinator will review each patient and their hemodialysis records at two week intervals and record primary or secondary end-points. Patients who reach the primary outcome of catheter malfunction will also be followed for an additional one month period, or until either: 1) six consecutive successful hemodialysis sessions are achieved (defined as a mean blood flow of ≥ 300 ml/min at each run in the two week period), or 2) the catheter is removed. Extending the follow-up will enable documentation of the natural history of the catheter after an episode of malfunction, and will allow an assessment of the costs associated with maintaining patency for the economic analysis. A time period of six successful hemodialysis sessions was chosen as recurrent malfunction typically occurs within two weeks of the initial malfunction [13]. Study drug may be discontinued for reasons of patient safety, or as requested by the patient. In these instances, the rt-PA will be discontinued but patients will be followed for study outcomes for the full six month study period. Reasons for discontinuation of study drug are outlined in Table 4.

**Table 4 T4:** Reasons for Discontinuing Patient Study Drug

• Started anticoagulation therapy
• Major hemorrhage, defined as bleeding resulting in a drop in hemoglobin greater than 20 g/L or bleeding requiring blood transfusion with other clinical evidence or suspicion of bleeding
• Undergone major surgery
• Diagnosis of intraspinal or intracranial neoplasm
• Patient decision to withdraw
• Active pericarditis
• Missed two or more consecutive weekly study treatment sessions

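### Fisher's test on crude bacteremia proportions ignores censored and possibly arm-dependent time at risk; the planned rate test corrects for this, but its level depends on independent infections

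*Protocol article*

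**What the plan says.** The protocol article's Statistical analysis section names two comparisons for bacteremia, the only secondary outcome.

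- For the proportion of patients infected: "Differences in proportions will be assessed using the Fisher's exact test".
- For the rate: "the number of infections per 1000 catheter days using the exact binomial test".

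Four other statements determine time at risk and the number of episodes a patient can contribute.

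- Study withdrawal, for both outcomes: "Therefore patients will be censored and withdrawn from follow-up at the following points in time: removal of the catheter". Transfer away and death also end follow-up.
- Secondary outcome, after an infection: "These patients will remain in the study and their catheter-related infection will be treated by the attending staff nephrologist according to usual practice". However, "If a new catheter is clinically indicated the patient will be censored at the time of catheter removal".
- Patient follow-up procedures: "Patients who reach the primary outcome of catheter malfunction will also be followed for an additional one month period", or until six successful sessions in a row or catheter removal.
- Sample size considerations assumes an "annual dropout rate of 75" per cent, with 95% or 98% of heparin patients malfunctioning within a year.

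The primary outcome, under the same censoring, is analysed by Kaplan-Meier and Cox methods.

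**The concern.** A crude proportion compares arms fairly only if both are observed for similar lengths of time. Here many patients leave early. If follow-up stops soon after malfunction, an effective lock keeps its patients under observation longer and gives them more days in which to become infected. Fisher's test would read those extra days as extra risk. It could then miss a real reduction in bacteremia, or suggest harm where there is none.

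The rate comparison divides by catheter-days and so avoids this problem. Its own weakness is different. An exact binomial test treats every infection as an independent event, whereas an infected patient who keeps the catheter can be infected again, and patients differ in risk. If repeats are counted, the test may reject too often.

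**Working it through.** **1. Check the planning model against Table 5.** Take exponential times, six months of follow-up, effect size as 1 − HR and two-sided α of 0.05 (sidedness is not stated).

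- Malfunction hazard, heparin: −ln(0.05) = 2.996 per year. Dropout hazard: −ln(0.25) = 1.386 per year.
- Event probability: h/(h + d) × [1 − exp(−0.5(h + d))]. Heparin: 2.996/4.382 × (1 − 0.112) = 0.607. With HR 0.667: 1.998/3.384 × (1 − 0.184) = 0.482. Mean 0.544.
- Freedman events: (1.960 + 0.842)² × (1.667/0.333)² ≈ 197. Patients: 197/0.544 ≈ 362, or 181 per arm. Table 5 gives 185.

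Across Table 5 the formula gives 230/181/162/120 (stated 235/185/160/120) and 200/158/141/104 (stated 195/160/140/95). Log-rank simulation at the stated sizes gives power of 0.80 to 0.82 in all eight cells. The model is therefore a fair stand-in for the trial's own planning.

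**2. Time at risk by arm.** If follow-up stopped at malfunction, mean time would be [1 − exp(−0.5(h + d))]/(h + d): 0.888/4.382 years = 74 days on heparin and 0.816/3.384 years = 88 days on rt-PA. Simulation with follow-up after malfunction (HR 0.667) gives 83 and 95 days with two weeks, and 91 and 101 with one month. At 6.5 infections per 1000 days in both arms and two weeks of follow-up, the expected proportions infected are 0.38 on heparin and 0.42 on rt-PA, although the true rates are equal.

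**3. Fisher's test against the alternatives.** Simulated with 170 per arm, independent infections and 2.5 to 6.5 infections per 1000 days (the range in the Background). Assumed: malfunction HR 0.65; where follow-up is truncated, half of malfunctions followed 14 days and half 30 days. This gives about 86 (heparin) and 98 (rt-PA) days at the 95% malfunction rate. False harm means a significant result with rt-PA worse (nominal 2.5%).

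| Scenario | Fisher | Log-rank, first episode | Planned rate test |
|---|---|---|---|
| No bacteremia effect, 95% malfunction, truncated: false harm | 6–10% | 2–3% | two-sided error about 5% |
| No bacteremia effect, 50% malfunction, truncated: false harm | 2–4% | – | – |
| Bacteremia HR 0.65, 95% malfunction, truncated: power | 15–27% | 37–67% | 39–79% |
| Bacteremia HR 0.65, follow-up not truncated: power | 37–63% | 47–78% | – |

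Without truncation, Fisher's two-sided error is 3 to 4%, so the bias disappears but the power loss remains.

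**4. The exact binomial test.** With independent infections its type I error is 4.4 to 5.4%. Now let patients' infection rates vary (gamma, mean 1; the variances 1 and 2 are assumptions) and count repeats. With HR 0.667, one month of follow-up after malfunction and no catheter removed for infection:

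| Infections per 1000 days | Variance 1 | Variance 2 |
|---|---|---|
| 2.5 | 7.2% | 10.2% |
| 6.5 | 14.6% | 23.2% |

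If half of infected catheters are removed, 14.6% falls to 8.4%. If all are removed, so that only first episodes count, the error is about 4 to 7%. A rate ratio with patient-level robust variance stays at 4.6 to 6.0% in the four tabulated settings.

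**The case against.** The strongest reply is that the plan already contains the remedy. The catheter-day rate uses exposure directly, holds its level when infections are independent, and in step 3 is as powerful as the log-rank test or more so. This stands. A reader might infer that the plan as a whole would hide a bacteremia benefit; that is true only of the Fisher comparison, and only if the rate result is set aside.

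Second, truncation after malfunction is inferred. Malfunction is not among the listed censoring points, and the follow-up section speaks of a six-month period and of extending follow-up. Ending within about a month is the natural reading, since the extra month and its stopping rules would otherwise have little purpose, but it is not explicit. The bias also needs a real effect on malfunction. The Background's figure of about fifty per cent catheter failure in a year leaves little bias. These limits stand; the power loss does not depend on them.

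Third, a reader might conclude that the binomial test is inflated. The article does not say that repeat episodes are counted. That follows only from its reference to a number of infections and from patients staying in the study. Neither the between-patient variance nor the share of infected catheters removed is given, so only a possible inflation can be claimed.

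A reader might also object that the two tests omit the randomisation strata, or that no rule says which one prevails. A condensed article may leave both to the full protocol or the SAP, so neither is a fault here.

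**Conclusion.** The concern holds for Fisher's test and conditionally for the binomial test. Fisher's test on crude proportions is a poor fit to this follow-up scheme. At a bacteremia HR of 0.65 it gives up roughly 10 to 15 percentage points of power to the log-rank test without truncation, and about 20 to 40 points with truncation at the 95% malfunction rate. Its bias against rt-PA (false harm of about 6 to 10%) rests on three things together: truncated follow-up, a malfunction HR near 0.65, and malfunction as frequent as planned.

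The rate comparison is sound for exposure. Its type I error could exceed 5% if repeats are counted, by an amount the documents do not allow one to fix. The matter is confined to a secondary outcome; the primary analysis and the 170 per arm are untouched.

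**What to change.** - Test bacteremia as time from randomisation to first definite or probable episode, by log-rank or Cox, censored at catheter removal and the other stated end points of follow-up.
- Keep infections per 1000 catheter-days as the supporting comparison. If repeat episodes are counted, use a patient-clustered robust variance, or a negative binomial model with log catheter-days as offset.
- Report the crude proportions infected descriptively, without Fisher's test.

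The cost is a change of analysis wording. Coordinators already record end-points at two-week reviews, and catheter-days are needed for the rate already planned, so no new data collection or change in sample size follows.
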